### Statistical methods

All randomised participants with valid 0 and 16-week observations will be included in the primary analysis (modified intent-to-treat analysis). The primary outcome will be analysed using generalised estimating equation (GEE), using an identity link function and normal distribution, to test the between-group differential change in DASS-21 total score from baseline to 16 weeks follow-up between the intervention and control groups. This will be estimated through two-way interaction between group allocation and follow-up time points in a GEE model that includes nominal intervention allocation factor, nominal measurement time and the two-way interaction between allocation and measurement time. In order to account for within-participants’ autocorrelation due to repeated measurements, Huber/White cluster sandwich variance estimates will be used to account for clustering from the same study participants [72]. As a secondary analysis, an additional GEE model will be implemented that includes all observations with at least one post-baseline measure. All other secondary longitudinal continuous outcome analyses will follow the same method as the primary outcome analysis. Sensitivity analysis may be used to evaluate missing at random assumptions for missing follow-up data. This will be done by imputing data assuming missingness is positively or negatively associated with outcomes in the intervention and control group and then the intervention effect sizes will be estimated from these different imputation scenarios. An additional sensitivity analysis will be performed with a GEE model adjusted for baseline measurements as potential covariates. Exploratory post hoc subgroup analyses may also be conducted if feasible to explore possible moderation of intervention effects (e.g. menopause status). Cross-sectional associations of baseline demographic and prognostic variables (e.g. habitual diet, exercise, personality, biomarkers) will also be explored. This work will be independent to the main trial report and will be conducted subject to further funding and staff resourcing.

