### Participant timeline

Figure 1 provides a schematic diagram of enrolment, interventions and assessments. Participants will complete three study visits (weeks 0, 4, 16) in addition to completing fortnightly assessments online (see Table 2). Participants will also collect their dairy products at two of these visits (weeks 0 and 4) and return to the study centre to collect additional products at week 10.

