**ASSESSMENTS (INSTRUMENT)**											
Psychological distress (DASS-21)			✓	✓	✓	✓	✓	✓	✓	✓	✓
Severity of depressive symptoms **(**PHQ-8)			✓^a^	✓	✓	✓	✓	✓	✓	✓	✓
Gastrointestinal symptoms (VAS-IBS)			✓	✓	✓	✓	✓	✓	✓	✓	✓
Stool formation (BSFS)			✓	✓	✓	✓	✓	✓	✓	✓	✓
Functional gastrointestinal disorders (ROME IV module)			✓								✓
Cognitive assessments (Cogstate)			✓								✓
Self-reported health/adverse effects				✓	✓	✓	✓	✓	✓	✓	✓
Perceived wellbeing (WHO-5)			✓								✓
Quality of life (AQoL-8D)			✓								✓
Self-reported health care utilisation (Resource use questionnaire)			✓								✓
Sleep (Athens Insomnia Scale)			✓								✓
Dietary intake (DQES v3.2)			✓								✓
Physical activity (IPAQ-SF)			✓								✓
Personality disorders screener (SAPAS)			✓								
Demographics (self-report)			✓								
Medications and dietary supplements (self-report)			✓								✓
Medical conditions and history (self-report)			✓								✓
Anthropometrics (stadiometer, weighing scales, measuring tape)			✓								✓
Body composition (DXA)			✓								✓
Gut microbiota (faecal, 16s RNA faecal analysis, metagenomics^b)^			✓		✓						✓
Markers of immune functions (blood, mesoscale discovery platform)			✓		✓						✓
Metabolomics – BCM-7 (blood, HPLC coupled to MS)			✓		✓						✓
Metabolomics – SCFA (faecal, GC-MS^b^ or HPLC analysis of faeces)			✓		✓						✓
Markers of oxidative stress (blood, glutathione assay kits)			✓		✓						✓

^a^Also completed at online pre-screening prior to preliminary baseline assessments

^b^Dependent on further funding

^c^In-clinic assessment

*AQoL-8D* Assessment of Quality of Life 8D, *BSFS* Bristol Stool Form Scale, *DASS-21* Depression Anxiety Stress Scale 21 items, *DQES* Dietary Questionnaire for Epidemiological Studies, *DXA* dual-energy X-ray absorptiometry, *HPLC* high-performance liquid chromatography, *IPAQ-SF* International Physical Activity Questionnaire short form, *MS* mass spectrometry, *GC-MS* gas chromatography-mass spectrometry, *PHQ-8* Patient Health Questionnaire 8-items, *SAPAS* Standardised Assessment of Personality Abbreviated Scale, *VAS-IBS* Visual Analogue Scale for Irritable Bowel Syndrome, *WHO-5* World Health Organization Wellbeing Index 5-items

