## Trial status

Recruitment for the RCT commenced in January 2019 and data collection was due to be completed by December 2020. The trial was halted in March 2020 due to social distancing regulations in response to the COVID-19 global pandemic. The trial team plans to resume recruitment upon easing of COVID-19-related restrictions in 2021. Amendments to the protocol may be employed to minimise face-to-face contact with trial participants. Any amendments will be updated on the ANZCTR.

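### The primary analysis keeps only women with a week-16 DASS-21 score, which sets aside about 11 of 90 randomised women and can bias the contrast if drop-out follows change in distress differently by arm

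*Protocol article*

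**What the plan says.** All of the analysis rules are in the Statistical methods section of the protocol article.

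- Primary set: "All randomised participants with valid 0 and 16-week observations will be included in the primary analysis (modified intent-to-treat analysis").
- Primary model: "The primary outcome will be analysed using generalised estimating equation (GEE), using an identity link function and normal distribution", with allocation, nominal time and their interaction. Within-woman correlation is handled through the variance: "Huber/White cluster sandwich variance estimates will be used to account for clustering from the same study participants". No weights are described and no working correlation is named.
- Wider set, as a secondary analysis only: "an additional GEE model will be implemented that includes all observations with at least one post-baseline measure".
- Missing data: "Sensitivity analysis may be used to evaluate missing at random assumptions for missing follow-up data". The scenarios described let missingness be positively or negatively related to outcome in each group.

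Table 2 shows what is collected. The row "Psychological distress (DASS-21") is ticked at weeks 0, 2, 4, 6, 8, 10, 12, 14 and 16, and the Participant timeline section confirms clinic visits "in addition to completing fortnightly assessments online (see Table 2"). The Intervention period section says that the week-16 questionnaires are emailed and completed online. The Power calculation section expects 12.5% attrition and inflates 80 women to 90.

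**The concern.** Baseline is measured before randomisation, so the condition that bites is having a week-16 score. A woman who answers every questionnaire to week 14 and misses the last emailed form leaves the primary analysis with her seven interim scores unused. The label suggests an intention-to-treat analysis, but the set is one of completers, and completers are no longer protected by randomisation. If the women who leave differ in their course of distress, and differ in another way in the other arm, the headline contrast moves away from the effect in all randomised women.

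The two other planned analyses do not change that headline. One is secondary and the other may not be run. Recruiting more women if attrition is high, as the Power calculation section allows, restores precision but does not remove selection.

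**Working it through.** **The plan's own figures.** Inputs from the Power calculation section: difference 2.3, SD of change 3.6, standardised effect 0.63, two-sided 0.05, 80% power.

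- n per arm = 2 × (1.960 + 0.842)² × (3.6/2.3)² = 38.5, so 39. With 0.63: 2 × (1.960 + 0.842)² / 0.63² = 39.6, so 40.
- t-test power at 40 per arm: 0.806 (2.3/3.6) and 0.795 (0.63). The stated design reproduces.
- 80 × 1.125 = 90. (80/0.875 = 91.4, a difference of no weight here.)

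**Women set aside.** 0.125 × 90 = 11.25, so about 11 are excluded and about 79 remain. Weeks 2 to 14 give seven interim scores.

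**Why arm-specific loss matters.** In an arm with loss d, completer mean change C and leaver mean change L, the mean over all women is (1 − d)C + dL. The completer mean is therefore off by d(C − L). The contrast is off by the difference of this quantity between arms.

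- Same d and same gap in both arms: the terms cancel and the bias is 0.
- d = 0.125 and a gap in one arm only: 0.125 × 1.8 = 0.225 and 0.125 × 3.6 = 0.45 points.
- Gaps in opposite directions double these to 0.45 and 0.90.

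**Simulation.** Nine fortnightly scores, 200,000 women per arm, SD of change 3.6, permanent drop-out with a logistic hazard on the last observed score or change. Assumed, and not in the document: baseline SD 6 or 10, hazard slopes of 1 to 1.5 per SD, everyone attends week 2. Loss is about 12.5% per arm unless stated. Each cell gives the result for baseline SD 6 / 10. GEE here means the unweighted all-data model with independence working correlation. MAR means sequential regression on the interim scores.

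| Drop-out follows | True effect | Completers | GEE, independence | MAR |
|---|---|---|---|---|
| Change, same in both arms | 0 | 0.02 / 0.00 | 0.01 / 0.01 | 0.02 / 0.00 |
| Change, same in both arms | −2.3 | −2.21 / −2.24 | −2.24 / −2.28 | −2.29 / −2.32 |
| Change, same, about 25% loss | −2.3 | −2.15 / −2.15 | −2.19 / −2.18 | −2.30 / −2.30 |
| Change, control only | −2.3 | −1.96 / −1.95 | −2.07 / −2.06 | −2.30 / −2.29 |
| Change, control only | 0 | 0.35 / 0.33 | 0.25 / 0.23 | 0.00 / −0.02 |
| Change, opposite by arm | 0 | 0.66 / 0.66 | 0.47 / 0.46 | −0.02 / −0.02 |
| Level, same in both arms | −2.3 | −2.29 / −2.30 | −2.18 / −2.16 | −2.31 / −2.30 |
| Level, control only | −2.3 | −2.17 / −2.24 | −1.22 / −0.66 | −2.29 / −2.30 |

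A second simulation, with a random intercept and slope per woman and a true effect of −2.3, gave for completers −2.04 / −2.02 (change, control only) and about −1.55 (change, opposite by arm). The completer errors under change-driven, arm-specific loss thus run from 2.30 − 2.04 = 0.26 to 2.30 − 1.55 = 0.75 points.

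**Effect on power.** With 40 per arm and SD 3.6, power is 0.806 at 2.3, 0.77 at 2.2 and about 0.67 at 1.95.

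**The secondary GEE.** Its result depends on the working correlation. In the second simulation, with level-driven loss in control only, independence gave −1.49 / −1.00, exchangeable −2.24 / −2.24 and unstructured −2.23 / −2.22.

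**The case against.** Several counter-arguments have force.

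- A reader might infer that the contrast is biased whenever drop-out depends on distress. The working does not support that. With a common mechanism the bias is nil under the null and at most about 0.15 points at the planned effect. The larger figures need drop-out that follows change and differs by arm, and no section documents such loss.
- Some features make it less likely. The trial is triple-blind, the products are described as equivalent, controls stay on a type of dairy they already drink, and established lactose intolerance or milk allergy excludes a woman. Against this, the Background section itself proposes effects of A1 beta-casein on the gut and on mood pathways, and the Adverse events section allows withdrawal for significant events. Arm-specific loss is therefore possible, though not shown.
- A reader might conclude that the secondary GEE is worse than the completer analysis. That holds only for independence working correlation. The article names none, and a full analysis plan may. With a suitable structure the all-data GEE comes close to a missing-at-random analysis.
- A reader might take the Trial status sentence "The trial was halted in March 2020 due to social distancing regulations" as evidence of informative loss. It reports an administrative stop, and the week-16 DASS-21 is online, so a clinic closure need not lose it.
- The plan already includes an all-data GEE, a baseline-adjusted GEE and scenarios for informative missingness. This is fair credit, but all of them sit beside a primary estimate that stays with completers, and the scenarios need not be run.

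**Conclusion.** The point holds in a limited form. The primary set is conditioned on having the week-16 outcome and leaves out about 11 of 90 randomised women at the planned attrition, with their interim data. The possible bias is roughly 0.25 to 0.75 points, or 11% to 33% of the planned 2.3, if drop-out follows change in distress and differs by arm. It is 0 to 0.15 points if the mechanism is common. These sizes rest on assumed drop-out slopes, baseline SDs and correlation structures. The documents give none of these, so the figures show what could happen and do not forecast it.

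The documents do not support the stronger conclusion that the randomised comparison is lost or that the result will be materially biased. The case for change is that the protective data are collected anyway, and analyses using them under missing at random stayed within about 0.02 points of the truth in the tabulated runs. Those runs generated drop-out from observed scores, so loss that depends on unobserved distress still needs the sensitivity scenarios. Severity: should-fix.

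**What to change.** 1. Make the primary analysis all randomised women as allocated, using baseline and every fortnightly DASS-21 score with a method valid under missing at random, and with allocation by week 16 as the primary contrast. A likelihood-based repeated-measures model with a simpler covariance structure stated in advance would do. Multiple imputation or a weighted GEE would also serve.
2. Do not simply promote the secondary GEE as it is described. If a GEE is kept, state its weights or working correlation.
3. Keep the week-0/week-16 completer GEE as a sensitivity analysis.
4. Make the informative-missingness scenarios mandatory and define them as departures from the new primary analysis.

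The cost is a change of wording in the protocol, analysis plan and registry. No new data are needed, and the Trial status section shows recruitment unfinished, so the change can precede unblinding. The downside is reliance on a covariance or imputation model. An unstructured covariance over nine visits has 9 × 10 / 2 = 45 parameters from about 90 women, which is why the fallback must be fixed beforehand.

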## Methods

### Trial design and setting

The Moo’D Study is a 16-week, superiority, parallel group, triple-blinded (i.e. participants, trial research team and study statistician), randomised, controlled trial conducted at the University Hospital Geelong, Australia. The study will randomise participants with 1:1 allocation ratio to either the intervention group (A2 beta-casein only dairy products) or the control group (conventional dairy products). The trial protocol has been prospectively registered with the Australia and New Zealand Clinical Trials Registry (ANZCTR; registered 17/12/18, ACTRN12618002023235) and was developed in accordance with the Standard Protocol Items: Recommendations for Interventional Trials (SPIRIT) statement [40]. The study has received ethical approval from the Barwon Health and Deakin University Human Research Ethics Committees (HREC) and will be conducted in accordance with the International Conference on Harmonisation (ICH) Guidelines for Good Clinical Practice (GCP) and will be reported using the Consolidated Standards of Reporting Trials (CONSORT) statement [41].

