### Randomisation

Following the completion of study visit 1, participants will be randomly assigned, on a 1:1 ratio, to receive either the A2 beta-casein only (A, intervention) or conventional dairy products (B, control) using stratified permuted block randomisation. Four strata will be constructed based on two variables: age (18–49, 50–75) and mood (PHQ-8 scores: 5–14; 15–24). An unblinded research assistant will use a computer-generated randomisation programme to generate a randomisation table using random block sizes, which will be partitioned by four strata based on the age and PHQ-8 scores.

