### Power calculation

To date, no studies have investigated the effects of A2 beta-casein only vs conventional dairy products on symptoms of psychological distress. For this reason, the anticipated effect size is largely based on findings derived from the broader nutrition literature [67–71]. A feasible sample size of 80 participants (40 per study arm) has been calculated to detect a medium intervention effect size of 0.63 (standard mean differences) defined as a between-group standard mean difference in DASS-21 total score from baseline to 16 weeks between the intervention and control groups. We assume the standard deviation of DASS-21 score change is 3.6, which is similar to published RCTs [67–69]. A sample size of 80 participants, achieves 80% power for a two-tailed analysis with a type I error level of 0.05 to detect a between-group mean difference of 2.3 or greater in DASS-21 total score from baseline to 16 weeks between the intervention and control groups. The total sample size will be inflated to 90 to account for an anticipated attrition rate of 12.5%. If our attrition rate is higher than anticipated (e.g. due to COVID-19 pandemic), we will aim to recruit further participants.

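### The primary GEE is an unadjusted comparison of change: baseline DASS-21 is adjusted for only in a loosely worded sensitivity analysis, the randomisation strata are named in no model, and some precision is lost

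*Protocol article*

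**What the plan says.** All references are to the protocol article.

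- **Statistical methods, primary model.** The purpose is "to test the between-group differential change in DASS-21 total score from baseline to 16 weeks follow-up between the intervention and control groups". The terms are listed: "a GEE model that includes nominal intervention allocation factor, nominal measurement time and the two-way interaction between allocation and measurement time". Robust (sandwich) variances handle the repeated measurements.
- **Statistical methods, analysis set.** "All randomised participants with valid 0 and 16-week observations will be included in the primary analysis (modified intent-to-treat analysis").
- **Statistical methods, baseline adjustment.** "An additional sensitivity analysis will be performed with a GEE model adjusted for baseline measurements as potential covariates". The same section applies the primary method to the other longitudinal continuous outcomes.
- **Randomisation.** "Four strata will be constructed based on two variables: age (18–49, 50–75) and mood (PHQ-8 scores: 5–14; 15–24"). The Statistical methods section mentions neither factor.
- **Power calculation.** A difference of 2.3 points with an SD of change of 3.6 and 40 women per arm "achieves 80% power for a two-tailed analysis with a type I error level of 0.05".

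**The concern.** Baseline DASS-21 enters the primary model only as an outcome. Each arm has its own baseline mean, although randomisation makes the two equal in expectation, and the effect is obtained by subtracting those means. Unless baseline and week 16 are almost perfectly correlated, subtracting the whole baseline value carries more noise into the estimate than regressing on it. It also passes chance baseline differences straight into the result.

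The strata raise a related point. The design treats age band and PHQ-8 band as prognostic enough to balance on, but the stated analysis does not use them. Leaving prognostic strata out tends to make the standard error larger than it need be.

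At stake is precision in a trial planned at about 80% power with 40 women per arm, and in the secondary outcomes that follow the same method.

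**Working it through.** **1. The plan's own figure.** Inputs from Power calculation: difference 2.3, SD of change 3.6, 40 per arm, two-sided 0.05. The standardised difference is 2.3/3.6 = 0.639. Noncentral-t power at 40 per arm is 80.6%; with the stated effect size of 0.63 it is 79.5%. The normal approximation needs 39 or 40 per arm. The stated 80% is reproduced, and it uses the SD of change, so it matches the unadjusted test.

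**2. What the primary model estimates.** The mean model is saturated in arm and time, and every analysed woman has both week-0 and week-16 values. The week-16 interaction is therefore the difference in mean change. In simulated two-time data, the GEE interaction and the raw difference in change were both −2.113, under independence and exchangeable working correlation. With nine visits and 15% of intermediate values missing, both were −3.401.

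**3. Effect of adjusting for baseline.** Let S be the DASS-21 SD, equal at both times, and rho the baseline to week-16 correlation.

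- Var(change) = 2S²(1 − rho)
- Var(week 16 given baseline) = S²(1 − rho²)
- Ratio = (1 + rho)/2
- Adjusted SD on the plan's scale = 3.6 × √((1 + rho)/2)
- Implied S = 3.6/√(2(1 − rho))

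The documents give neither rho nor S. The values of rho below are assumptions.

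| rho | variance ratio | adjusted SD | implied S | power, 40 per arm |
|---|---|---|---|---|
| unadjusted | 1 | 3.60 | – | 80.6% |
| 0.5 | 0.75 | 3.12 | 3.60 | 90.3% |
| 0.7 | 0.85 | 3.32 | 4.65 | 86.4% |
| 0.8 | 0.90 | 3.42 | 5.69 | 84.5% |
| 0.9 | 0.95 | 3.51 | 8.05 | 82.5% |
| 0.95 | 0.975 | 3.55 | 11.38 | 81.5% |

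**4. Which rows fit the plan.** The same relation can be run the other way, with the SD of change held at 3.6: rho = 1 − 3.6²/(2S²). An assumed S of 5, 6, 8 or 10 gives rho of 0.74, 0.82, 0.90 or 0.94, and power of 85.6%, 84.1%, 82.5% or 81.8%. The DASS-21 total runs from 0 to 63 (Primary outcome measure) and the women enter with PHQ-8 scores from 5 to 24 (Randomisation). An SD below 5 would be narrow for that population, so the lower rows of the table are the more plausible.

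**5. Unequal variances.** If the week-16 SD is 1.2 times the baseline SD, power is 85.6% at rho 0.5 and 81.9% at rho 0.7. The gain shrinks but does not reverse.

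**6. Whether the planned sensitivity analysis recovers the precision.** In the simulated two-time data (rho 0.5), adding baseline as a covariate while it also stayed an outcome row changed nothing: the SE was 0.667 with and without it. Regressing week 16 on arm and baseline gave 0.623. In the nine-visit simulation the figures were 0.732 with and without it, and 0.662. The sensitivity analysis helps only if baseline leaves the outcome vector or the arms share a baseline mean, and the article does not say which form is meant.

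**The case against.** The strongest defence is that the plan is coherent. Objective, primary outcome, model and sample size all concern change from baseline. Under randomisation the comparison is unbiased and its type I error is sound. Baseline adjustment is already planned, so the dispute is partly about which analysis is called primary. Stratification covariates might also be left to a statistical analysis plan that is not shown. All of this stands as a defence of validity. It does not answer the efficiency point, because the article itself lists the primary terms, and the adjusted analysis is neither primary nor specific about its covariates.

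A second objection concerns size and also stands. Correlations of 0.4 to 0.7 give power of 92% to 86%, and a reader might infer a gain of 6 to 12 points. Combined with an SD of change of 3.6, those correlations imply a DASS-21 SD of only 3.3 to 4.6. The documents do not support a gain of that size as the likely one.

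On the strata, PHQ-8 band and DASS-21 both measure mood, so their contributions overlap. Stratifying on PHQ-8 band also already limits gross imbalance in baseline mood. No figure in the documents shows how much variance the strata explain.

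**Conclusion.** The point holds as one of efficiency. The primary test is an unadjusted change comparison that gives up precision obtainable from data already collected, and it leaves the estimate open to chance baseline imbalance. With the plan's 2.3 and 3.6 at 40 per arm and equal variances, adjustment raises power from 80.6% to between about 82% (rho 0.95) and 90% (rho 0.5). The likely gain under the plan's figures is a few points, and it would be larger if the true correlation is lower. Any gain from the strata is additional, unquantified and partly shared with baseline DASS-21.

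Three stronger readings do not follow:

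- That the result would be biased or the trial wrongly sized. The test is valid and the sample size calculation matches it.
- That baseline is never adjusted for. A sensitivity analysis does so, though its wording may yield no gain.
- That omitting the strata gives false positives. The omission tends to make the inference conservative.

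**What to change.** Make one of these the primary model:

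- post-baseline DASS-21 as the outcome, with baseline DASS-21 and its interaction with time as covariates; or
- baseline kept as an outcome, with the two arms constrained to a common baseline mean.

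In either case, include the age band and PHQ-8 band used in randomisation. Name these covariates outright instead of calling them potential, and state that baseline is not both a covariate and an unconstrained outcome row. Keep the present change model as a sensitivity analysis. Apply the same approach to the secondary longitudinal continuous outcomes.

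The cost is small. Age, PHQ-8 and DASS-21 are all collected at week 0, so no new data are needed. The change takes a few sentences in the analysis plan, plus a protocol amendment and a registry update, and it must be made before unblinding.

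### Added as main effects to the stated allocation-by-time GEE, baseline covariates leave the primary-set week-16 effect and its robust standard error unchanged, so the planned adjusted sensitivity analysis tests nothing

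*Protocol article*

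**What the plan says.** All of this stands in one paragraph, Statistical methods in the protocol article.

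- Primary set: "All randomised participants with valid 0 and 16-week observations will be included in the primary analysis (modified intent-to-treat analysis".
- Model: "The primary outcome will be analysed using generalised estimating equation (GEE), using an identity link function and normal distribution".
- Mean structure: it "includes nominal intervention allocation factor, nominal measurement time and the two-way interaction between allocation and measurement time". Week 0 is therefore part of the response.
- Effect: "This will be estimated through two-way interaction between group allocation and follow-up time points in a GEE model".
- Standard errors: "Huber/White cluster sandwich variance estimates will be used to account for clustering from the same study participants". The working correlation is not named.
- Secondary set: "an additional GEE model will be implemented that includes all observations with at least one post-baseline measure".
- Adjusted analysis: "An additional sensitivity analysis will be performed with a GEE model adjusted for baseline measurements as potential covariates".

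The last sentence does not mention covariate-by-time terms, does not take week 0 out of the response, and does not name the women to be analysed. The Randomisation section stratifies by age and PHQ-8, but the primary model contains neither.

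**The concern.** The treatment effect is a within-woman contrast, week 16 against week 0, compared between arms. Baseline DASS-21, age and baseline PHQ-8 each have one value per woman. Entered as a main effect, such a covariate raises or lowers her fitted values equally at every visit and drops out of the contrast. With baseline DASS-21 there is the further oddity that the same number is both the week-0 response and a predictor.

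This sentence is the only baseline-adjusted estimate of the treatment effect that the article plans. With about 40 women per arm, some chance difference in baseline distress is plausible, and a reader would look to this analysis to see whether it mattered. If the adjusted result must equal the primary result whatever the data, the agreement carries no information, yet it could be taken as evidence of robustness.

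**Working it through.** **Inputs.** The model, primary set and sandwich errors come from Statistical methods. The 40 per arm, SD of change 3.6 and difference 2.3 come from Power calculation. The working correlation is not given, so several were tried.

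**The plan's own figure.** n per arm = 2 x (1.960 + 0.842)^2 x 3.6^2 / 2.3^2 = 2 x 7.851 x 12.96 / 5.29 = 38.5, so 39 by the normal approximation and 40 by the t-test. Power at 40 per arm is 81.5% (normal) or 80.6% (t). The stated 80 reproduces and does not depend on this point.

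**Algebra.** Let r(i,t) = Y(i,t) - mu(g,t) - gamma'x(i) be the residual of woman i in arm g at visit t, with x(i) fixed at baseline.

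1. Under an exchangeable working correlation, the estimating equation for arm g and visit t is: sum over women seen at t of [r(i,t) - c(i) R(i)] = 0. Here R(i) is her residual total and c(i) depends only on her number of visits. Independence is the case c(i) = 0.
2. In the primary set the same women are seen at weeks 0 and 16. Subtracting the two equations gives: sum over arm g of [r(i,16) - r(i,0)] = 0.
3. In r(i,16) - r(i,0) the term gamma'x(i) cancels. So mu(g,16) - mu(g,0) is the mean change in arm g, and the interaction is the arm difference in mean change, with or without x.
4. The sandwich variance of that contrast is the sum over arms of sum[D(i) - Dbar(g)]^2 / n(g)^2, where D(i) is the woman's change and n(g) the number of women in the arm. It contains no x either. At the plan's own figures the standard error is 3.6 x sqrt(2/40) = 0.805 in both models.

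**Numerical check.** Simulated data, 40 women per arm, nine visits, Gaussian identity-link GEE with robust errors; illustrative only.

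| Model, primary set | Week-16 effect | SE |
|---|---|---|
| Stated model | -3.02386351 | 1.06005763 |
| + baseline DASS-21 | -3.02386351 | 1.06005763 |
| + baseline DASS-21, age, PHQ-8 | -3.02386351 | 1.06005763 |
| + baseline DASS-21 by time | -2.7504 | 1.0712 |
| + age and PHQ-8 by time | -3.0289 | 1.0864 |
| Week-16 ANCOVA on baseline DASS-21 | -2.7504 | 1.0712 |
| Week-16 ANCOVA on baseline DASS-21, age, PHQ-8 | -2.6168 | 1.0325 |

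The first three rows agree with weeks 0 and 16 only and with nine complete visits, under independence, exchangeable and unstructured working correlation. They also agree with 15% of intermediate visits missing, under independence and exchangeable. An unstructured correlation with missed intermediate visits was not checked.

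**Where equality ends.**

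- Secondary set with about 12.5% lacking week 16, unadjusted against adjusted for all three covariates: -1.697 (SE 1.018) against -1.862 (0.968) under independence; -1.975 (0.971) against -1.946 (0.968) under exchangeable.
- Four women dropped for a missing covariate: -3.340 (1.097). This reflects a change of women, not adjustment.
- Software that scales the robust variance by the parameter count: SE 1.0796 against 1.0819, estimate unchanged.

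**What an effective adjustment does.** With baseline DASS-21 as covariate, the estimate moves by (1 - b) x D0, where b is the within-arm slope of week 16 on baseline and D0 the chance baseline difference between arms. In the simulated data the move is -2.7504 - (-3.0239) = 0.2735. The document gives neither b nor D0.

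**The case against.** The strongest reply is that the article does not actually specify the empty model. It speaks of a GEE adjusted for baseline, not of the primary model plus main effects, and many statisticians would take that to mean post-baseline outcomes with baseline as covariate. The term structure, covariate list and analysis set of a sensitivity model are commonly left to the analysis plan, and only a condensed article is shown.

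Part of this stands. A reader might infer that the adjusted analysis can never differ from the primary one. The document does not support that, because the sentence is not tied to the primary set and does not exclude covariate-by-time terms or a change of response. In each of those cases the results can move. A reader might also infer a fixed shift or a fixed loss of precision. Neither can be claimed: both depend on the chance baseline difference and on the correlation between baseline and week 16, which the article does not give. In the simulated data, adjusting for baseline DASS-21 alone even raised the standard error slightly (1.0712 against 1.0601).

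What does not stand is that this is merely absent detail. The paragraph sets out one model with week 0 in the response and then adds covariates to a GEE. An analyst who follows the text in order would fit the empty version.

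**Conclusion.** The point holds conditionally. If baseline covariates enter as main effects in the stated allocation-by-time GEE, in women all observed at weeks 0 and 16, the week-16 interaction is unchanged. So is its sandwich standard error, apart from a trivial parameter-count correction. This was shown algebraically for independence and exchangeable working correlation, and numerically for unstructured correlation with complete visits. On that natural reading, the only planned baseline-adjusted treatment estimate gives no information on baseline imbalance and no gain in precision.

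The primary estimate, its standard error, the type I error and the sample size of 80 are not affected. It would be wrong to infer from this that the primary analysis is invalid. The fault lies in a supporting analysis and is worth correcting because the correction is easy.

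**What to change.** Replace the sentence with an explicit model, in one of two forms.

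1. Post-baseline DASS-21 (weeks 2 to 16) as the response; allocation, nominal time and their interaction; baseline DASS-21 and the stratification variables age and PHQ-8 as covariates. State that the effect is the between-arm difference at week 16. An interaction measured against the first post-baseline visit would again cancel time-constant covariates.
2. The stated model with week 0 kept in the response, plus covariate-by-time terms for baseline DASS-21, age and PHQ-8.

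Name the analysis set. Using the primary set means that any difference from the primary result comes from adjustment and not from a change of women; a repeat in the secondary set can be added. Age and PHQ-8 are needed for stratification and baseline DASS-21 for entry to the primary set, so no woman should be lost for a missing covariate.

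The cost is a change of wording in the protocol or analysis plan. All the data are already collected, and the sample size stays as it is.
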